# At-risk registers integrated into primary care to stop asthma crises in the UK (ARRISA-UK): study protocol for a pragmatic, cluster randomised trial with nested health economic and process evaluations

**DOI:** 10.1186/s13063-018-2816-z

**Published:** 2018-08-29

**Keywords:** At-risk asthma, General practice, Pathway of care, Register, eLearning, Hospitalisation

## Abstract

**Background:**

Despite effective treatments and long-standing management guidelines, there are approximately 1400 hospital admissions for asthma weekly in the United Kingdom (UK), many of which could be avoided. In our previous research, a secondary analysis of the intervention (ARRISA) suggested an improvement in the management of at-risk asthma patients in primary care. ARRISA involved identifying individuals at risk of adverse asthma events, flagging their electronic health records, training practice staff to develop and implement practice-wide processes of care when alerted by the flag, plus motivational reminders. We now seek to determine the effectiveness and cost-effectiveness of ARRISA in reducing asthma-related crisis events.

**Methods:**

We are undertaking a pragmatic, two-arm, multicentre, cluster randomised controlled trial, plus health economic and process evaluation. We will randomise 270 primary care practices from throughout the UK covering over 10,000 registered patients with ‘at-risk asthma’ identified according to a validated algorithm. Staff in practices randomised to the intervention will complete two 45-min eLearning modules (an individually completed module giving background to ARRISA and a group-completed module to develop practice-wide pathways of care) plus a 30-min webinar with other practices. On completion of training at-risk patients’ records will be coded so that a flag appears whenever their record is accessed. Practices will receive a phone call at 4 weeks and a reminder video at 6 weeks and 6 months. Control practices will continue to provide usual care. We will extract anonymised routine patient data from primary care records (with linkage to secondary care data) to determine the percentage of at-risk patients with an asthma-related crisis event (accident and emergency attendances, hospitalisations and deaths) after 12 months (primary outcome). We will also capture the time to crisis event, all-cause hospitalisations, asthma control and any changes in practice asthma management for at-risk and all patients with asthma. Cost-effectiveness analysis and mixed-methods process evaluations will also be conducted.

**Discussion:**

This study is novel in terms of using a practice-wide intervention to target and engage with patients at risk from their asthma and is innovative in the use of routinely captured data with record linkage to obtain trial outcomes.

**Trial registration:**

ISRCTN95472706. Registered on 5 December 2014.

**Electronic supplementary material:**

The online version of this article (10.1186/s13063-018-2816-z) contains supplementary material, which is available to authorized users.

## Background

Worldwide, asthma affects 334 million people [1]. In the UK, which has one of the highest prevalence rates in Europe, there are 5.4 million patients with asthma, and asthma affects one in five households [2]. A quarter of all asthma patients have poor symptom control [3] and 185 people are admitted to hospital because of asthma attacks every day in the UK [2]. Asthma attacks result in major social, psychological and healthcare costs. For example, attacks are associated with a doubling of the healthcare costs for managing severe asthma in both children and adults [4, 5]. Asthma is, therefore, a common condition which results in a large, unnecessary personal, healthcare and economic burden [6]. Worryingly, given that there are an increasing number of effective treatments and long-standing, evidence-based management guidelines for asthma [7], the death rate for asthma has not reduced over recent years [8].

It is widely accepted that the majority of deaths and hospital admissions from asthma are associated with preventable factors [9]. In 2012, this prompted a National Review of Asthma Deaths (NRAD) [10], which showed that poor access to care and poor adherence with preventive medication(s) were key contributors in the deaths of a large proportion of patients. Patient-assessed poor access to primary care is also associated with emergency hospital admissions for asthma [11]. Unfortunately, due to complicating clinical and psychosocial characteristics, patients with asthma who are at particular risk of attacks (at-risk asthma) often fail to attend routine appointments or engage in initiatives [12], such as self-management education, that improve outcomes in general asthma populations [13]. In addition, these patients characteristically under-use primary care services, often fail to attend scheduled appointments [14, 15] and have difficulty adhering to treatments [16, 17]. It is these same patient groups that are also most often excluded from clinical trials. Existing evidence is thus unlikely to be generalisable [18] and research is urgently needed to identify better management strategies for this group. Systematic nationwide training and implementation programmes, mostly based in primary care, are able to reduce the morbidity and impact of asthma with reduced costs [19]. Also, a clinical care pathway for children with asthma has been shown to modify practice behaviour and reduce emergency department attendance and hospitalisations, but not significantly so, compared to usual care [20]. Indeed, the current British Thoracic Society/Scottish Intercollegiate Guideline Network (BTS/SIGN) British guideline on the management of asthma notes that ‘*well-conducted studies are needed to define the benefits of care pathways for asthma. These should include large, suitably powered studies to clarify the impact of pathways promoting systematic management of people with high-risk asthma in UK primary care’.* [7]

In an observational pilot study at a single primary care practice [21], electronic flagging of the electronic health records (EHRs) of 26 patients, demonstrating characteristics previously associated with adverse asthma outcomes, and training all practice staff in appropriate actions to take on seeing the flag was associated with a reduction in the number of emergency events for asthma in these individuals over 1 year, compared to 26 age-, sex- and treatment-matched controls. Our subsequent regional cluster randomised trial involving 29 primary care practices in Norfolk [22] covering 911 people at a high-risk of experiencing asthma crisis events (at-risk asthma, defined in line with contemporaneous guidelines as severe asthma plus adverse psychosocial factors) similarly flagged patients’ EHRs and delivered a 1-h practice-based training session for practice staff. The intervention did not reduce the primary composite endpoint of asthma attacks [23, 24] over 1 year. However, increases in the number of prescriptions of prednisolone (31% (95% confidence interval (CI) − 8 to 85)) masked reductions in the percentage of hospitalisations (50% (95% CI 6 to 74)) and accident and emergency (A&E) attendances (26% (95% CI − 31 to 58) amongst patients in intervention versus control practices. The intervention was well received by practice staff (according to an exit questionnaire) and resulted in an estimated cost-saving of £138.21 (95% CI £1248 to − £910) per patient in the intervention arm.

This regional study suggested that our primary care intervention for at-risk asthma patients (ARRISA) may have potential as a strategy for improving practice-level management and reducing emergency admissions, near-fatal asthma and asthma deaths, in this group. However, it remains to be seen whether these findings would translate into a meaningful clinical benefit at a larger scale. Furthermore, the identification of at-risk individuals in the previous studies was achieved by manually searching records to provide evidence of adverse psychosocial factors and the training was undertaken via a face-to-face, practice-based group discussion led by an experienced facilitator. These features of the intervention would be difficult to roll out nationally so we modified these processes in our current study: individuals with at-risk asthma will be automatically identified using a computer code containing details of an algorithm based on data routinely available in primary care EHRs and the training will be delivered via an online eLearning platform and webinars. Furthermore, in contrast to the original study where outcome data were obtained by semi-manually searching the primary care EHRs, in the current study we will utilise anonymous data extraction and record linkage of primary and secondary care records.

The study aims to test the hypothesis that systematically identifying patients at risk of severe exacerbations of asthma, flagging their primary care EHR to provide enduring prompts at the time of contacts with the practice, training all practice staff about the systematic management of these patients and providing on-going practice support (hereafter referred to as creation and integration of a primary care at-risk asthma register) will reduce crisis asthma events (asthma-related deaths, hospitalisations and A&E attendances) for at-risk patients and be clinically acceptable and cost-effective without detriment to the care of non-at-risk asthma patients.

Our intervention operates at the practice level. A cluster randomised trial design is, therefore, appropriate with the general practice as the unit of randomisation. As such, although the majority of objectives (including primary endpoint) and the health economic analysis pertain to the participant level, some objectives pertain to the cluster level (including aspects of the process evaluation). The study will be conducted in a controlled open study with blind assessment. The comparator will be usual care as defined by the current BTS/SIGN British Asthma Guideline [7] and National Institute for Health and Care Excellence (NICE) guidelines [25].

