## Methods

### Aims

The primary aim of this study is to determine whether the creation and integration of at-risk asthma registers into primary care, as conceptualised in our ’At-Risk Registers Integrated into primary care to Stop Asthma crises’ (ARRISA) intervention, reduces asthma-related crisis events (A&E attendances, hospitalisations and deaths) for *at-risk patients* over a 12-month period compared to control practices. Our secondary aims are to assess outcomes (time to first crisis event, asthma control, all-cause admission or death) for *all* patients with asthma; and also to examine changes in the processes of asthma care (treatments, vaccinations, use of action plans or smoking cessation services, adherence to treatment) within practices. We also aim to assess whether this intervention is acceptable to healthcare professionals and patients and cost-effective from the perspective of the National Health Service (NHS). We will identify characteristics that influence uptake, integration and effectiveness of the intervention and explore causal mechanisms leading to changes in outcomes, including any unanticipated effects.

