### Individual patients

Patients at recruited practices are included in the study if they have at-risk asthma as determined by our algorithm applied to routinely available primary care data forming the ‘original register’. Practice staff may add or remove patients from the register (see below), but the primary analysis will be conducted using data from all patients on the original register without additions or withdrawals. In addition, data from all patients with asthma defined on the basis of being on the practice asthma register will be included for the purpose of examining secondary outcomes.

Patients will be excluded if they have refused for their anonymous data to be used in research or are terminally ill and receiving palliative care. Patients have the right to refuse access to their data at any point until the conclusion of the data extraction.

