#### Secondary outcomes

The time to first, and rate of, asthma-related crisis event(s) (defined as above) for at-risk patientsThe percentage of all registered asthma patients with an asthma-related crisis event, their rate of, and time to, first asthma-related crisis event(s) (as above)The percentage of at-risk and all registered asthma patients with good control defined as answering ‘no’ to all of the RCP3Qs [29]The percentage of at-risk and all registered asthma patients requiring a hospital admission or dying for any reasonThe number of the following (per patient per year) for both at-risk and all registered asthma patients:

(a) short-acting bronchodilator prescriptions issued

(b) prescriptions of systemic corticosteroids for asthma attacks and antibiotic-treated lower respiratory tract infections

(c) modifications of the prescription of asthma-related medications to align more closely with current guidelines (e.g. increased use of inhaled corticosteroids)

(d) records of written personalised asthma action plans and patient self-monitoring with peak flow diaries

(e) inhaler technique assessments recorded

(f) smoking cessation advice or smoking cessation medications given

(g) flu vaccinations

(h) ‘did not attends’ at primary and secondary care routine appointments

(i) adherence to medication determined from validated computer-based calculations using prescription data

Health economic outcomes6.The estimated (per patient) mean incremental cost of the at-risk register compared with usual care7.The incremental effect of the at-risk register, in terms of the estimated (per patient) mean difference (between arms) in the number of asthma crisis events

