#### Safety outcomes

There will be no documentation or reporting of non-serious adverse events. Deaths and hospitalisation are the primary effectiveness outcome and will not be reported as safety measures. Practices will be asked to capture complaints or important study-related adverse events by completing a complaints/adverse events form and forward it to the Norwich Clinical Trials Unit (NCTU).

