### Data collection

#### Baseline characteristics and outcome data

All practices expressing interest in the study are asked to complete an initial questionnaire to provide basic data on practice characteristics.

All participating practices must agree to share their practice EHRs with Optimum Patient Care (Cambridge, UK). Obtaining data in this way not only permits linkage to different databases (practice EHRs, Office for National Statistics (ONS), Hospital Episode Statistics (HES)), but also permits data capture without burdening the practice or patients. All practices (control and intervention) are asked to insert a specific Read code that cannot be readily removed by practice staff into the EHRs of at-risk asthma patients to denote inclusion in this study. This will be used by data managers and statisticians to identify these patients and distinguish their data from other patients with active asthma in the practice. For the purposes of data collection, active asthma is defined using the QOF criterion [27]: Read code for asthma diagnosis plus asthma therapy in the past year, excluding those coded as asthma resolved but not excluding QOF exception codes. At the end of the study, data extractions will be obtained for all patients with asthma in the practice containing data for the 12 months before randomisation and the 12 months following the activation of the flag in the intervention practices. The mean time from randomisation to activation of the flag will be calculated for all intervention practices, and data collection will be captured for 12 months from this time after randomisation in the control practices. For clinical event data and for patients’ demographic and other characteristics (weight, height, smoking status, etc.) the last recorded value will be obtained.

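### The no-detriment part of the hypothesis has no matching patient-level analysis: outcomes are set for at-risk and for all registered asthma patients, and the second group contains the first

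*Protocol article*

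**What the plan says.** The hypothesis at the end of the Background section has two clinical parts: fewer crisis events in at-risk patients, and that the intervention will "be clinically acceptable and cost-effective without detriment to the care of non-at-risk asthma patients".

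The analysis populations in the rest of the article are these:

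- **Aims:** "Our secondary aims are to assess outcomes (time to first crisis event, asthma control, all-cause admission or death) for" all patients with asthma.
- **Individual patients:** besides the at-risk patients found by the algorithm, "data from all patients with asthma defined on the basis of being on the practice asthma register will be included" for secondary outcomes. At-risk patients are not excluded from this wider group.
- **Primary outcome:** at-risk patients only.
- **Secondary outcomes:** crisis events in at-risk patients and the "percentage of all registered asthma patients with an asthma-related crisis event"; "The percentage of at-risk and all registered asthma patients with good control"; all-cause admission or death in the same two groups; and prescribing and care-process counts "for both at-risk and all registered asthma patients".
- **Additional subgroup analyses:** three variations, on patients staying on the register, training completion, and patients added to the register.

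The Safety outcomes section states: "Deaths and hospitalisation are the primary effectiveness outcome and will not be reported as safety measures".

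Under Baseline characteristics and outcome data, records are extracted for every asthma patient in practices of both arms, and a Read code lets statisticians "identify these patients and distinguish their data from other patients with active asthma in the practice".

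**The concern.** The intervention asks staff to give flagged patients priority, both through the suggested flag wording and through the reminder videos. If staff time and appointments are limited, the obvious unwanted effect is that unflagged asthma patients get less. The no-detriment clause of the hypothesis addresses that risk.

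No listed patient-level result addresses it directly. The nearest one, for all registered asthma patients, pools the group targeted for benefit with the group that could be harmed. Effects in opposite directions then cancel, and the better the intervention works in at-risk patients, the more harm elsewhere the pooled figure can absorb. At stake is one clause of the stated hypothesis; the primary result is unaffected.

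The Safety outcomes section adds a smaller problem. Its reason for not treating deaths and hospitalisations as safety measures is that they are the primary outcome. The primary outcome covers asthma-related events in at-risk patients only, so the reason does not extend to other patients or to other causes.

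**Working it through.** **1. The plan's own figure.** The Sample size section gives 8204 patients from 235 practices, for 7% versus 5%, 90% power, cluster size 35 and ICC 0.01. Assuming a two-sided 5% level (not stated in the article) and a continuity correction, the requirement is 3061 per arm before clustering. The design effect is 1 + (35 − 1) × 0.01 = 1.34. Then 2 × 3061 × 1.34 = 8203.5, and 8203.5 / 35 = 234.4 practices. The figure reproduces, and it concerns at-risk patients only. The article gives no size for any other group.

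**2. Size of the offset per practice.** Inputs from the article: 39 at-risk patients per practice (10,530 / 270) and the planned fall from 7% to 5%. Assumed: the number of non-at-risk asthma patients per practice, m.

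- Events removed among at-risk patients: 39 × 0.02 = 0.78 per practice.
- Rise among the others that leaves the pooled count unchanged: 0.78 / m.

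| Assumed m | Offset rise (percentage points) |
|---|---|
| 200 | 0.39 |
| 400 | 0.195 |
| 800 | 0.0975 |

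A relative increase also needs an assumed base rate. With m = 400 and 0.8%, it is 0.195 / 0.8 = 24%. Over m from 200 to 800 and base rates from 0.5% to 1%, it runs from 0.0975 / 1 = 10% to 0.39 / 0.5 = 78%.

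**3. The same in terms of the at-risk share.** If at-risk patients are a share f of all asthma patients, a 2-point benefit cancels a harm of 2f / (1 − f) points. This is 0.11 points at f = 5%, 0.22 at 10%, 0.50 at 20% and 0.86 at 30%. Check at f = 10% with an assumed non-at-risk rate of 1%:

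- Control: 0.1 × 7 + 0.9 × 1.00 = 1.60%.
- Intervention: 0.1 × 5 + 0.9 × 1.22 = 1.60%.

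The pooled rates agree while the non-at-risk rate has risen by 22% in relative terms.

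**4. What a separate comparison could show.** At f = 10% a practice has 390 asthma patients, 351 of them non-at-risk, and there are 135 practices per arm. For 1.00% versus 1.22% at a two-sided 5% level:

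- ICC 0.01: design effect 1 + 350 × 0.01 = 4.5, effective size 135 × 351 / 4.5 = 10,530 per arm, power about 34%.
- ICC 0.001: design effect 1.35, effective size 35,100 per arm, power about 80%.

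The share, the rate and the ICC in this group are all assumptions. The comparison may be informative or imprecise, which is a reason to report an interval.

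**The case against.** - **The data allow the test.** A reader might infer that the hypothesis cannot be tested at all. The article does not support that: non-at-risk records are extracted in both arms and the Read code separates them. What is missing is the specification.
- **The masking shows itself.** Both at-risk and all-patient results are planned, so a clear benefit in the first with no difference in the second would make a careful reader suspect harm in the rest, and crude percentages follow by subtraction. This stands in part. Subtraction does not by itself give a cluster-adjusted interval, and the comparison would be chosen after the results are seen. The article also nowhere says that a no-detriment conclusion will rest on the pooled result, so it would be wrong to claim that it will.
- **The events are reported.** A reader might take the Safety outcomes section to mean that deaths and admissions among non-at-risk patients go unreported. They do not: all-cause admission or death is a combined secondary outcome for at-risk and for all registered patients. It is simply not shown for the non-at-risk group.
- **Other work bears on displacement.** The process evaluation looks at practice procedures and unintended consequences, so not every outcome is tied to the two patient groups. It is not a comparison of patient outcomes by arm.
- **It may be in the analysis plan.** A margin or model detail may well be there, and its absence here is no fault. The mismatch between hypothesis and outcome populations is within this article.
- **Intervention practices can add patients.** Some patients outside the original register will then be flagged. Defining the group by the original register still respects randomisation, because control practices have no equivalent additions to remove.

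**Conclusion.** The point holds in this form: the article states a no-detriment hypothesis for non-at-risk patients, and no listed patient-level outcome or further analysis matches it. The all-patients outcomes are a poor substitute, because a benefit in at-risk patients can offset harm in the others.

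The size is illustrative. With the planned 2-point benefit and an assumed 400 non-at-risk patients per practice, the offset is about 0.2 percentage points; for 200 to 800 such patients it is about 0.4 to 0.1. The relative increase depends further on an assumed base rate, so the 10% to 78% range is not an estimate for this trial. The offset also requires the benefit to occur. Without it, the pooled difference at 400 such patients would be 400 / 439 = 91% of the difference in non-at-risk patients, so little would be hidden.

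The reason given in the Safety outcomes section is too broad, but the events themselves are analysed. This should be corrected; it does not threaten the primary analysis.

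**What to change.** 1. Add an analysis population: registered asthma patients not on the original at-risk register, with membership fixed in the same way in both arms and unaffected by later additions or removals.
2. Report in it, by arm, crisis events, all-cause admission or death, and the main care-process outcomes, using the clustered models already planned.
3. Base any statement on detriment on the effect estimate and confidence interval in this group. Neither the pooled result nor a non-significant test should carry it.
4. Reword the Safety outcomes section so that its reason is limited to asthma-related events in at-risk patients, and point to the secondary outcome that covers all-cause admission or death.

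The cost is some wording and a few extra model runs on data that are already to be extracted. The downside is a secondary comparison that was not separately powered; it should be labelled as such.
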